# The effect of systemic antidepressant treatments in early stage on neurocognitive function of euthymic bipolar patients initiated with a depressive onset: An observational, cross‐sectional, single‐blind study protocol

**DOI:** 10.1002/brb3.2360

**Published:** 2021-09-14

**Keywords:** antidepressant treatment, bipolar disorder, euthymic state, neurocognitive function

## Abstract

**Objectives:**

Patients with bipolar disorder (BD) have a wide range of neurocognitive dysfunction even in euthymic state, leading to impaired psychosocial function and reduced quality of life. However, the understanding on risk factors related to neurocognitive impairment in such group of people is limited. In view of significantly delayed diagnosis of BD and common use of antidepressants prior to the BD diagnosis, the study aims to clarify whether systemic antidepressant use in early stage, defined as from the initial depressive episode to the diagnosis of BD, could impact neurocognitive function of euthymic bipolar patients.

**Methods:**

It is an observational, cross‐sectional, single‐blind trial, making a comparison in neurocognitive function between euthymic bipolar patients who had a depressive episode as initial onset and being with and without systemic antidepressant treatments in early stage (*n* = 62 and 62, respectively); secondary outcomes include the impact of systemic antidepressant use on global function, quality of life, sleep quality, positive and negative affect, and peripheral level of neuron‐specific enolase.

**Discussion:**

The study will provide a comprehensive and in‐depth understanding on the effect of systemic antidepressant treatments in early stage in such group of patients. It is expected to better guide the related prevention and treatment work of BD management.

**Trial Registration:**

The study was registered on Clinicaltrials.gov with protocol ID (TJAH2020‐18) and clinicaltrials.gov ID (NCT04564573).

## BACKGROUND

1

Bipolar disorder (BD) is a severe chronic disorder characterized by depressive episodes and alternating or intertwining manic and hypomanic episodes, with a lifetime prevalence rate exceeding 1% worldwide (Clemente et al., 2015). BD can result in a wide range of neurocognitive dysfunctions, mainly involving attention, verbal learning, nonverbal memory, and executive functions (Douglas et al., 2018; Kurtz & Gerraty, 2009). The neurocognitive dysfunctions could occur in very early stage of illness and persist even in euthymic period (Sole et al., 2017), which causes severe damage to individual psychosocial function and significantly increases disease‐related burden (Alonso et al., 2011). Therefore, alleviating neurocognitive dysfunction and accordingly improving patients’ psychosocial function and quality of life have become a critical goal of BD management (Grande et al., 2017). To this end, some clinical studies have attempted to improve the neurocognitive function of patients with BD pharmacologically and psychotherapeutically, but the outcomes are far from satisfaction (Sole et al., 2017). One of the reasons could be that the understanding on the risk factors related to neurocognitive impairment in such group of people is limited. Theoretically, a comprehensive and in‐depth understanding of relevant risk factors will help to better guide the prevention and treatment work of BD.

About 50% of BD initiates its expression in the form of depressive episode (Drancourt et al., 2013; Tondo et al., 2010), in which only 20% can get a diagnosis of BD within the first year of onset (Hirschfeld et al., 2003), and the average delay from first episode to diagnosis of BD is 5–10 years (Baldessarini et al., 2007). The main reason for this significant delay is that a large number of bipolar patients do not experience any manic/hypomanic symptoms in the early stage, defined as a term from initial depressive onset to the diagnosis of BD, and the clinical manifestations of bipolar depression are highly similar to unipolar depressive episodes (Drancourt et al., 2013; Tondo et al., 2010). As a result, patients may receive systemic treatment with antidepressants for a long time because of the misdiagnosis or delayed diagnosis. The attitude regarding the effect of antidepressants used in early stage on neurocognitive function of patients with BD is controversial yet. Empirically, antidepressant treatment could deprave the natural course of disease and facilitate switching from depressive onset to episodes of mania, hypomania, or mixed state (Berkol et al., 2019; Sole et al., 2017; Viktorin et al., 2014), which may cause cognitive injury (Goodwin et al., 2008). For example, BD patients with higher number of manic and/or hypomanic episodes had a worse performance in Neurocognitive Composite Index (NCI), visual memory, and working memory (Sánchez‐Morla et al., 2019); furthermore, patients with BD, particularly those with multiple mood episodes, showed severe dysfunction in emotional memory than healthy controls (Fijtman et al., 2020). In addition, the number of manic episodes was positively correlated with level of 8‐hydroxy‐2 deoxyguanosine (8‐OHdG), a modulator of DNA methylation, which could be a potential mechanism underlying cognitive dysfunction (Soeiro‐de‐Souza et al., 2013). Consistently, studies have shown that antidepressant agents per se undermined the neurocognitive function of the elderly and increased the incidence of mild cognitive impairment or dementia (Leng et al., 2018; Moraros et al., 2017), which may contribute partly to the neurocognitive impairments in patients with BD. However, it is arguable to expand the view based on the evidence from bipolar depression to depressive episode prior to any mania/hypomania emergence. Furthermore, it has been illustrated that antidepressant treatment can improve cognitive performance (Brendel et al., 2018; Tunc‐Ozcan et al., 2019), although the evidence did not derive from studies focusing on bipolar patients specifically. In view of the high incidence of delayed diagnosis or misdiagnosis of BD (Tondo et al., 2010), the use of antidepressants in the early stage is quite common and extensive. Therefore, a further understanding in the relationship between antidepressant used in the early stage and neurocognitive function of bipolar patients has significantly scientific and clinical significance.

The current study attempts to clarify this question by making comparisons in neurocognitive function between bipolar patients who had a depressive episode as initial onset and being with and without systemic antidepressant treatment (received adequate dosage of antidepressants for 6 weeks at least) in early stage. Furthermore, the social functions and quality of life will also be investigated because both items are highly associated with cognitive functions and are indicative for functional rehabilitation. Apart from those, we will also study the influence of antidepressants used in early stage on impulsiveness, quality of sleep, and positive and negative affect. Lastly, peripheral neuron‐specific enolase (NSE) will be evaluated. NSE, a cell‐specific isoenzyme of glycolytic enolase, is known as a sensitive marker of neuronal damage (Isgrò et al., 2015). It has been showed that high level of serum NSE was related to mild cognitive dysfunction in patients with diabetic retinopathy (Yu et al., 2020) and that serum NSE levels of BD patients were significantly different from healthy controls (Akcan et al., 2018). In this regard, it is expected to examine the potential association between serum NSE level and cognitive function of BD patients. Finally, although it is mainly an explorative investigation and is informative for clinical practice regardless of outcomes, we expect that systemic antidepressant treatments in early stage could negatively affect the neurocognitive function, social functions, and quality of life of patients with BD.

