### Study design

2.1

This is a cross‐sectional study focusing on euthymic bipolar patients who had a depressive episode as initial onset. Participants were divided into two groups according to whether they had received systemic antidepressant treatment in the early stage: systemic antidepressant treatment (AT) group versus no systemic antidepressant treatment (NT) group.

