### Limitations

3.1

There are some limitations of the current study. First, some information, such as history of antidepressant treatment and first manic/hypomanic episode, is mainly derived from patients’ memory, which may lead to a recall bias. For another, we assume a systemic antidepressant treatment as a consecutive therapy with adequate dosage of antidepressants for 6 weeks at least, but regardless of the antidepressant types and dose differences, which may obscure the potential effect of specific type or dose of drug. Finally, there are no data available on standard deviations and effect size for neurocognitive function of targeted patients, therefore the putative sample size might increase the risk of type II error.

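### NT is only the complement of the AT definition, so it can contain antidepressant-exposed patients, and the chance of entering AT grows with diagnostic delay, which the analysis does not name as a factor.

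*Protocol article*

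**What the plan says.** Section 1 (Background) defines systemic treatment as having "received adequate dosage of antidepressants for 6 weeks at least". Section 3.1 (Limitations) describes it as "consecutive therapy with adequate dosage of antidepressants for 6 weeks at least", which adds that the weeks must be consecutive.

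Section 2.1 forms the groups "according to whether they had received systemic antidepressant treatment in the early stage", giving "systemic antidepressant treatment (AT) group versus no systemic antidepressant treatment (NT) group". Section 2.10 repeats this. NT has no definition of its own, and the criteria in sections 2.4 and 2.5 neither require NT patients to be antidepressant-naive in the early stage nor cap shorter or lower-dose use there.

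The early stage is "defined as a term from initial depressive onset to the diagnosis of BD". Section 1 reports that "the average delay from first episode to diagnosis of BD is 5–10 years" and that "only 20% can get a diagnosis of BD within the first year of onset". It also says that delayed or mistaken diagnosis is why patients may be on antidepressants for a long time.

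Section 2.9 collects age of onset and time of bipolar diagnosis. Section 2.19 lists factors for the between-group balance check. Age of onset and number of attacks are among them and the onset-to-diagnosis interval is not, but the list is open-ended. Only factors that differ significantly become covariates. A pooled multiple regression on each factor follows.

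**The concern.** Two problems follow from how the groups are formed.

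1. **Exposure within NT.** A patient with several short courses, or with long use below the adequate dose, is classed as NT. If such use has some of the effect of full treatment, the AT–NT contrast is smaller than the contrast between treated and untreated patients, and a null result is hard to read.
2. **Delay as a confounder.** A patient with years between first depression and bipolar diagnosis has many more chances to complete six adequate weeks than one diagnosed quickly. If longer undiagnosed illness is itself related to cognition, AT and NT can differ with no drug effect at all.

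The study's aim is to say whether early-stage antidepressant treatment affects cognition, so both problems bear on its main conclusion.

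**Working it through.** **1. The text side by side.** Two separate four-week courses at adequate dose total eight weeks. They could qualify for AT under the section 1 wording but would not under section 3.1, so the two wordings can put the same patient in different groups. Under either wording, partly exposed patients fall into NT. The window runs from onset to diagnosis, so its length equals the delay.

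**2. The plan's sample size as a starting point.** Section 2.6 gives n = 2[(t_α/2 + t_β/2)S/δ]² with α = 0.05, β = 0.20, δ = 0.3 and n = 62 per group; S is not stated. Using 1.960 + 0.842 = 2.802 (80% power):
- S = 1: n = 2(2.802/0.3)², which rounds up to 175.
- n = 62 requires S = 0.3 × √31 / 2.802 = 0.596, a standardised effect of 0.3/0.596 = 0.503.

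The stated inputs therefore do not yield 62 without an unstated S. That is a separate matter; here it only means that any baseline effect used below is an assumption.

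**3. What the significance screen can miss.** If delay were tested for balance, a true gap of g SD would be tested with 62 per group at two-sided 0.05. The noncentrality is g√(62/2), and the probabilities come from the noncentral t with 122 df:

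| True delay gap (SD) | Flagged | Missed |
|---|---|---|
| 0.2 | 20% | 80% |
| 0.3 | 38% | 62% |
| 0.4 | 60% | 40% |
| 0.5 | 79% | 21% |

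These figures need only n = 62 and α = 0.05 from the plan, plus the assumed gap.

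**4. Effect of leaving delay unadjusted (assumed inputs).** Suppose no drug effect, a delay gap of g SD and a slope of b SD of cognition per SD of delay. The spurious difference is g × b:

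| Gap | Slope | Spurious difference | Rejection rate at nominal 5% |
|---|---|---|---|
| 0.3 | 0.2 | 0.06 | 6.3% |
| 0.3 | 0.3 | 0.09 | 7.9% |
| 0.5 | 0.2 | 0.10 | 8.6% |
| 0.5 | 0.3 | 0.15 | 13.2% |
| 0.8 | 0.2 | 0.16 | 14.3% |
| 0.8 | 0.3 | 0.24 | 26.3% |

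These rates apply to a comparison with delay left out. A gap as large as 0.8 SD would usually be flagged if delay were screened, so the 0.8 rows matter mainly if delay is never put on the list.

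**5. Effect of exposure within NT (assumed inputs).** If a share f of NT carries a fraction r of the full effect in the same direction, the observed effect is d(1 − f·r). Taking d = 0.50, power is 79% with 62 against 62. Removing the exposed patients leaves about 50 in NT at f = 0.2 and about 43 at f = 0.3:

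| f | r | Observed d | Power, all NT | Power, NT restricted |
|---|---|---|---|---|
| 0.2 | 0.25 | 0.475 | 75% | 74% |
| 0.2 | 0.5 | 0.45 | 70% | 74% |
| 0.3 | 0.25 | 0.4625 | 72% | about 70–71% |
| 0.3 | 1 | 0.35 | 49% | about 70–71% |

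Restriction can gain or lose power depending on r. Its case is a clearer contrast, not a dependable gain in power.

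**The case against.** **Delay is partly covered already.** Both components are collected, the factor list in section 2.19 is open-ended, number of attacks is named, and a full covariate list is detail that an article may leave to a document not shown. This stands in part: delay may yet be examined. But the rule that is printed makes adjustment depend on a significance test, and step 3 shows how unreliable that is at this sample size.

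**The article already admits limitations.** Section 3.1 concedes recall bias, and says treatment is counted "but regardless of the antidepressant types and dose differences". That concerns differences between drugs and doses; it says nothing about who may be in NT or how long the window is.

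**Adjusting for delay may be wrong.** Section 1 says antidepressants may promote switching to mania or hypomania, which could bring the diagnosis forward. Delay may then be partly a consequence of exposure. This stands, and is why the adjusted result should not replace the unadjusted one.

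**Stronger readings that the documents do not support:**
- *AT status is tied by construction to a long delay.* Strictly, only an early stage shorter than six weeks rules out AT. Beyond that the link is plausible and supported by section 1, but it is empirical.
- *The two biases act in opposite directions.* That requires a harmful drug effect. The article calls the evidence controversial and cites benefit too. If the true effect is beneficial, exposure within NT and longer illness in AT could both pull the estimate toward zero.
- *Power falls to about 49%.* That needs 30% of NT to be exposed and to carry the full effect, from a d of 0.50 that the plan does not set. With δ = 0.3 and S = 1, power is already about 38% with no dilution.
- *No result could be attributed to antidepressants.* Part of that is the general limit of a cross-sectional observational study that the article describes as mainly exploratory.

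**Conclusion.** The point holds in a limited form, as something that should be changed. From the text alone, NT may include patients with early-stage antidepressant exposure, opportunity to enter AT grows with diagnostic delay, and section 2.19 does not secure adjustment for that delay. An AT–NT difference could therefore reflect longer undiagnosed illness, and a null result could reflect exposure within NT.

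The size of either bias is unknown. The documents give no share of partly exposed NT patients, no effect of sub-threshold use, no expected delay gap between the groups and no slope of cognition on delay. The firmest number is the screen's miss rate: 62% for a 0.3 SD gap and 21% for a 0.5 SD gap. The rejection rates of 8.6% to 13.2% for a 0.5 SD gap rest on assumed slopes of 0.2 to 0.3, and the dilution figures illustrate only.

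**What to change.** 1. **Reconcile the definition.** Make sections 1 and 3.1 agree on whether the six weeks must be consecutive, and state in section 2.1 what early-stage antidepressant use NT permits. Cost: wording.
2. **Prespecify a delay-adjusted analysis.** In section 2.19, add an analysis adjusted for the onset-to-diagnosis interval whatever the balance test shows, reported beside the analysis without it. The interval comes from data already collected. Downside: possible over-adjustment if antidepressant-induced switching shortens the interval, which is why both results are shown.
3. **Add a sensitivity analysis on NT.** Record any early-stage antidepressant use, compare AT with NT patients who had none, and show partly exposed patients separately. The treatment history is already taken and checked against records and guardians (section 2.11), so this is a small addition to the form. Downside: fewer patients and less precision in the restricted comparison.

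Two further options add less. Requiring an early stage of at least six weeks in NT would probably remove few patients, given that only 20% are diagnosed even within the first year, and would leave opportunity very unequal. Cumulative weeks of use as an exposure term would lean on the recall that section 3.1 already lists as a weakness.

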## METHODS/DESIGN

2

### Study design

2.1

This is a cross‐sectional study focusing on euthymic bipolar patients who had a depressive episode as initial onset. Participants were divided into two groups according to whether they had received systemic antidepressant treatment in the early stage: systemic antidepressant treatment (AT) group versus no systemic antidepressant treatment (NT) group.

### Setting

2.2

All procedures will be performed in Tianjin Anding Hospital.

### Population

2.3

This study will consist of a sample of 124 patients with BD (AT group vs. NT group: 62 vs. 62) recruited from outpatient and inpatient departments of Tianjin Anding Hospital.

### Inclusion criteria

2.4

Patient's inclusion criteria are as follows: (1) diagnosisof BD according to the Diagnostic and Statistical Manual of Mental Disorders, Fourth Edition (DSM‐IV‐TR) with Structured Clinical Interview for DSM‐IV (SCID); current state of euthymia is defined by both scores of Montgomery–Åsberg Depression Scale (MADRS) and Young Manic Rating Scale (YMRS) < 7 (Cullen et al., 2016), lasting for 4 weeks at least before recruitment; (2) initiated with a depressive episode diagnosed with the MINI‐International Neuropsychiatric Interview (MINI); (3) age between 18 and 50 years; (4) participants comply with all procedures of study; and (5) participants must sign informed consent.

### Exclusion criteria

2.5

Patient's exclusion criteria are as follows: (1) history of psychotic symptoms; (2) comorbidity of attention deficit and hyperactivity disorder; (3) neurological trauma or neurological diseases that could cause cognition injury; (4) history of substance dependence/abuse; (5) received modified electroconvulsive therapy in the past 12 months; (6) severe physical disease affecting cognitive function or increasing peripheral NSE; (7) recent drug use that affects cognition, such as tricyclic antidepressants, anticholinergic drugs, amphetamines, and so forth, (8) IQ < 70; and (9) use of benzodiazepines 4 h before scale evaluation.

### Sample size calculation

2.6

There are no data available on effect size and standard deviations specific for cognitive function of targeted patients, therefore power calculation remains speculative. For the value of *δ*, we assume that it should come out between 0.25 and 0.5, and we set it as 0.3. With formula *n*
_1_ = *n*
_2_ = 2 × [(*t*
_α/2_ + *t*
_β/2_) *S*/*δ*]^2^, setting *α* at 0.05 and *β* at 0.20 in a two‐tailed independent *t*‐test indicated that a minimum of 62 patients per group is needed (totally 124 participants).

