### Withdrawal of subjects

2.18

Subjects can quit the study at any time for any considerations without any consequences. The investigator can decide to withdraw subjects from the trial if the subjects are not compliant with the study procedures or any conditions emerge that violate the inclusion/exclusion criteria during processing. All withdrawals will be excluded from the study and new participants will be recruited.

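### Section 2.6: 62 patients per group does not follow from δ = 0.3, α = 0.05 and β = 0.20; if δ is a standardised effect, power at 0.3 is about 38%, and if it is a raw difference the power cannot be verified

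*Protocol article*

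**What the plan says.** Section 2.6 of the protocol article opens by conceding a gap: "There are no data available on effect size and standard deviations specific for cognitive function of targeted patients". For δ it continues "we assume that it should come out between 0.25 and 0.5, and we set it as 0.3". It gives neither a unit nor an endpoint for δ.

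It then prints n₁ = n₂ = 2 × [(t_α/2 + t_β/2) S/δ]² for a two-tailed independent t-test, with the error rates fixed by "setting *α* at 0.05 and *β* at 0.20", and states that this "indicated that a minimum of 62 patients per group is needed". No value of S is given.

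Section 2.3 repeats the split, "AT group vs. NT group: 62 vs. 62". Section 2.18 replaces withdrawals ("All withdrawals will be excluded from the study and new participants will be recruited"), so no dropout allowance is built into 62. The only later comment is in section 3.1, which says that "the putative sample size might increase the risk of type II error".

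**The concern.** The article prints the inputs, the formula and the result together, so a reader should be able to get from one to the other. That is not possible. One required input, S, is absent, and the obvious default (δ in SD units, S = 1) gives a number nearly three times as large. The formula also carries t_β/2 where a sample size for power 1 − β uses t_β.

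At stake is the meaning of the stated minimum of 62. A reader will take it to mean 80% power at the effect the authors chose. If δ is standardised, an effect of that size would be missed more often than found. The calculation is the only quantitative support for the sample size, so it should reproduce or say what it rests on.

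**Working it through.** **Inputs.** From section 2.6: two-sided α = 0.05, β = 0.20, δ = 0.3 (assumed range 0.25 to 0.5), independent two-group t-test. From section 2.3: equal groups of 62. S is not stated. I take S = 1 for the standardised reading and solve for S on the raw reading. Normal quantiles: 1.960 for α/2, 0.8416 for β = 0.20, 1.2816 for β/2 = 0.10.

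**1. Trying to reproduce 62.** Set n = 62 and δ = 0.3 and solve for S = δ√(n/2)/(z_α/2 + z_power):

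- with t_β: 0.3 × √31 / 2.8016 = 1.6703 / 2.8016 = 0.596
- with t_β/2 as printed: 1.6703 / 3.2415 = 0.515

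Neither value appears in the article. With t_β, S = 0.59, 0.595 and 0.60 give 61, 62 and 63 per group. So 62 can be reached only by supplying an S that the document does not give.

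**2. The formula with δ standardised (S = 1).**

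- t_β: 2 × (2.8016 / 0.3)² = 174.4, so 175 per group (exact t-test 176)
- t_β/2 taken literally, which means 90% power: 2 × (3.2415 / 0.3)² = 233.5, so 234 per group (exact 235)

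Other variants at δ = 0.3 do not give 62 either: one-sided 80% power needs 138, one-sided 90% needs 191, and a one-sample or paired formula needs 88 (one-sided 69).

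**3. What 62 per group delivers on the standardised reading** (exact two-sided t-test, α = 0.05):

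| Standardised difference | Power with 62 per group |
|---|---|
| 0.25 | 28% |
| 0.30 | 38% |
| 0.40 | 60% |
| 0.50 | 79% |

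At 0.3 the normal approximation agrees: 0.3 × √31 = 1.670, 1.670 − 1.960 = −0.290, and Φ(−0.290) = 38.6%. The difference detectable with 80% power is 0.507, about 0.51 SD.

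**4. Raw reading.** If δ = 0.3 is in raw units, power depends entirely on S. By the normal approximation, 62 per group has 92% power at S = 0.5, 80% at 0.595, 73% at 0.65, 55% at 0.8 and 39% at 1.0. The document does not say where in this range, or outside it, the study lies.

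**5. Precision.** With 62 per group the unadjusted 95% confidence interval for a standardised difference has a half-width of about 1.98 × √(2/62) = 0.36 SD.

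**The case against.** The strongest defence is that the formula shows S separately from δ. If δ were already standardised, S would be redundant, so the printed form can be read as a raw difference with its own SD. With S near 0.60 the same inputs give 62 and about 80% power. The statement that no data exist is limited to the target patients, so an S borrowed from another population is not excluded, and an article may leave such a value to the full protocol. This part stands: a reader might infer that the study is shown to have 38% power, and the document supports that only on the standardised reading.

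The defence does not rescue the figure. Section 2.7 lists about ten main cognitive measures on different scales, and a single unitless δ for all of them makes sense mainly in SD units. On the raw reading, the printed inputs still do not yield 62. Covariate adjustment does not help either. The calculation is for a t-test, and shrinking S from 1 to 0.596 would need covariates explaining 1 − 0.596² = 64% of the variance, which the article nowhere claims.

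The article also calls its calculation speculative, describes the study as mainly explorative, and admits a type II risk. These caveats lower the harm, and nothing in the text says that a null result will be taken as proof of no effect. But they concern uncertainty about the true effect. They do not tell the reader that 62 fails to follow from the chosen δ.

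Two further inferences should be resisted:

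- **That 62 was computed at a standardised effect of 0.5.** The normal formula there gives 62.8, which rounds up to 63 (exact t-test 64). An S near 0.60 with δ = 0.3 fits as well. The document does not show how 62 arose.
- **That a null result could not rule out any effect below about 0.5 SD.** This confuses the effect detectable at 80% power with precision. With a half-width of about 0.36 SD, an estimate near zero would exclude 0.4 to 0.5 SD, though not 0.3.

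**Conclusion.** The point holds conditionally. What is certain is that 62 per group cannot be derived from the stated δ, α, β and formula, because S is missing and S = 1 gives 175 (or 234 with the formula as printed).

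How much power is lost depends on what δ means. If it is standardised, the more natural reading, power at the chosen 0.3 is about 38%, and at the upper end of the assumed range it is 79%, only one point short of 80%; the substantial shortfall is lower in the range. If δ is raw, power is unknown, neither shown to be adequate nor shown to be low. The power figures assume one unadjusted two-sided t-test with 62 evaluable patients in each group. The general caveats in sections 2.6 and 3.1 do not correct the number.

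**What to change.** Keep the sample at 124 and change the text.

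- **Section 2.6, formula:** replace t_β/2 with t_β.
- **Section 2.6, inputs:** choose one of two statements. Either say that δ is standardised, and that 62 per group gives 80% power (two-sided α = 0.05) for a difference of about 0.51 SD and about 38% power at 0.3. Or, if δ = 0.3 is a raw difference, name the endpoint, its scale and the S that yields 62, with the source or assumption behind that S.
- **Section 3.1:** replace the general remark on type II error with the figures that apply. On the standardised reading, add that a non-significant result would not show the absence of a 0.3 SD effect, given an unadjusted 95% confidence interval half-width of about 0.36 SD.

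This costs wording only, with no extra patients and no change of design. If δ is declared standardised, the stated detectable effect becomes less favourable than the present text implies.
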